## Abstract

**Background:**

Minimally invasive glaucoma surgery (MIGS) is a new class of surgeries, which combines moderate to high success rates and a high safety profile. Bent Ab interno Needle Goniotomy (BANG) and Gonioscopy-Assisted Transluminal Trabeculotomy (GATT) are two low-cost MIGS procedures that communicate the anterior chamber to Schlemm’s canal. Most of the available publications on MIGS are either case series or retrospective studies, with different study protocols. The aim of this manuscript is to describe a randomized clinical trial (RCT) protocol to compare the long-term intraocular pressure (IOP) control and the safety of both procedures in eyes with primary open-angle glaucoma.

**Methods:**

This is a parallel, double-arm, single-masked RCT that includes pseudophakic primary open-angle glaucoma (POAG) eyes. After inclusion criteria, medications will be washed out to verify baseline IOP before surgery. Patients will be randomized to BANG or GATT using a sealed envelope. Follow-up visits will be 1, 7, 15, 30, 60, 90, 180, 330 and 360 days after surgery. On PO330, a new medication washout will be done. The main outcome is the IOP reduction following the procedures. Complimentary evaluation of functional and structural parameters, safety, and quality of life will be done after 30, 90, 180, and 360 days.

**Discussion:**

Our study was designed to compare the long-term efficacy and safety of two low-cost MIGS. Most of the published studies on this subject are case series or retrospective cohorts, with different study protocols, which included different types and severities of glaucomas, combined with cataract extraction. Our study only included mild to moderate POAG eyes, with previous successful cataract extraction. Moreover, it provides a standardized protocol that could be replicated in future studies investigating various types of MIGS. This would allow comparison between different techniques in terms of efficacy, safety, and patients’ quality of life.

**Trial registration:**

Retrospectively registered at the Registro Brasileiro de Ensaios Clínicos (ReBEC) platform RBR-268ms5y. Registered on July 29, 2023.

The study was approved by the Ethics Committee of the University of Campinas, Brazil.

## Background

Glaucoma is the leading cause of irreversible blindness worldwide, affecting over 76 million people nowadays and 40 million more in the years to come [1]. Intraocular pressure (IOP) is the main risk factor related to glaucoma progression [2]. IOP can be controlled through the use of topical medications, laser, or surgery [3–5]. Filtering surgery, such as trabeculectomy, and glaucoma drainage device implantation are effective in reducing IOP, but may lead to severe intra- and postoperative complications [6, 7].

Minimally invasive glaucoma surgery (MIGS) emerges as a new class of surgeries, which may result in adequate IOP reduction, although still inferior to filtering procedures, with a high safety profile [8, 9]. MIGS can be divided into four types depending on the pathway activated by each one: suprachoroidal, subconjunctival, ciliary body, and Schlemm’s canal [8, 9].

Schlemm’s canal MIGS lowers the IOP by reducing the trabecular resistance to aqueous humor outflow through Schlemm’s canal and collector channels [10]. This can be achieved by a trabecular bypass, Schlemm’s canal dilation, or trabeculotomy. Bent Ab interno Needle Goniotomy (BANG) and Gonioscopy-Assisted Transluminal Trabeculotomy (GATT) [11] are two low-cost MIGS procedures that communicate the anterior chamber to Schlemm’s canal.

Most of the available publications on MIGS are either case series or retrospective studies, with different study protocols [11–23]. Moreover, these studies frequently include a variety of types of glaucoma, and cataract extraction is often combined with the MIGS procedure. Finally, none of these studies included the washout of antiglaucoma medications to verify the real IOP effect of the procedure [11–23]. The medication confounding factor prevents an objective interpretation and comparison of the postoperative results. The aim of this manuscript is to describe a randomized clinical trial (RCT) protocol to compare the long-term IOP-lowering effect and adverse effect profile of BANG and GATT in eyes with primary open-angle glaucoma.

## Methods

### Setting

This study is an ongoing parallel double-arm, single-masked RCT that includes pseudophakic primary open-angle glaucoma (POAG) eyes. The study is coordinated by the University of Campinas, São Paulo, Brazil, and patients are recruited at two centers in the country (Hospital de Clínicas da Unicamp, Campinas, São Paulo, Brazil, and Hospital Regional de Divinolândia, Divinolândia, São Paulo, Brazil). Patients’ eyes will be randomized to BANG or GATT by a sealed envelope at a 1:1 ratio. The group allocation is masked for the patient.

The primary outcome is the IOP reduction from baseline. Secondary outcomes are a reduction from baseline of medication use, adverse effects after the intervention, and functional, structural, and quality of life evaluation. Patients will be followed for at least 12 months. This article followed the SPIRIT guidelines for its elaboration [24].

### Inclusion and exclusion criteria

The following inclusion criteria are listed: (1) eyes with POAG, defined as an open angle on gonioscopy and structural loss detected by optic coherence tomography (OCT) and/or functional loss observed with visual field examination, (2) age between 40 and 80 years, (3) visual field mean deviation ≥  − 12 dB, (4) retinal nerve fiber layer thickness (RNFLT) ≥ 60 µm, (5) previous uneventful cataract surgery with intraocular lens implantation, (6) best corrected visual acuity (BCVA) ≥ 0.1 at the Snellen chart (LogMAR = 1), (7) IOP ≥ 18 mmHg measured in two occasions with the Goldmann applanation tonometer under a maximum of 3 IOP-lowering medications, and (8) IOP between 20 and 36 mmHg after medication washout.

Exclusion criteria are defined as: (1) secondary open-angle glaucoma (uveitis, corticoid-induced, pseudoexfoliation, pigmentary and juvenile), (2) primary or secondary angle-closure glaucomas, (3) phakic eyes or cataract surgery performed less than 30 days before inclusion, (4) previous glaucoma surgery (other MIGS procedures, glaucoma drainage devices, or cyclophotocoagulation), (5) previous vitreoretinal surgery, and (6) severe corneal opacity.

### Participant recruitment, initial procedures, and randomization

Patients will be recruited at two sites in Brazil. Medical personnel in both sites will be informed of inclusion and exclusion criteria and pre-screening patients who could be eligible for the study. Recruitment will be done by one of the three members of the research team on the same day. The first patient was enrolled in March 2022, and the protocol is still in the recruitment phase. Figure 1 summarizes the participants’ follow-up.

**Fig. 1 Fig1:**
[figure not shown]
Study flow chart. BANG, bent Ab interno needle goniotomy; GATT, gonioscopy-assisted transluminal trabeculotomy; IOP, intraocular pressure; RNFLT, retinal nerve fiber layer thickness; mGCL, macular ganglion cell layer; BMO-MRW, Bruch’s membrane opening – minimum rim width; MD, visual field mean deviation; ECD, endothelial cell density; NEI-VFQ-25, National Eye Institute Visual Field Function Questionnaire 25

At baseline, a complimentary evaluation will be done, including ultrasonic pachymetry and specular microscopy (Tomey EM3000, Tomey Corporation, Japan) to measure central corneal thickness and endothelial cell density, respectively; RNFLT, macular ganglion cell layer and Bruch’s membrane opening — minimum rim width measurements are obtained with OCT (Spectralis OCT, Heidelberg Engineering, Germany) for structural evaluation; 24–2 visual field tests using SITA-Fast (Humphrey Field Analyzer, Carl Zeiss Meditec AG, Germany) for functional evaluation; and quality of life assessment with the Brazilian validated version of the National Eye Institute—Visual Function Questionnaire-25 questionnaire [25].

After meeting all inclusion criteria at recruitment, patients will be invited to participate in the study. All procedures will be fully explained and an informed consent will be obtained by one of the three members of the research team. After that, patients will be asked to interrupt the use of all IOP-lowering medications and return after 30 days to measure the IOP. The IOP measured after medication washout will be considered the baseline IOP.

### Randomization and group allocation

Randomization will be done using an opaque sealed envelope containing the group (BANG or GATT) at a 1:1 ratio. The random allocation sequence will be generated by the operation room supervisor. The envelope will be opened moments before the surgery by the nurse in the operation room, which will enroll and assign participants for intervention. This study is single-masked for the participants. Double-masking is not possible for investigators, since gonioscopy could identify the surgical procedure postoperatively.

**Fig. 2 Fig2:**
[figure not shown]
Surgical steps of GATT. **A** A sectorial goniotomy is created with a 25-G needle to expose Schlemm’s canal; **B** the 5–0 Prolene wire is inserted in the canal and progressed 360° using a 23-G microforceps

BANG will be performed as described by Seibold et al. [26]. A 2.75-mm temporal main incision is created and hydroxypropyl methyl cellulose 4% is injected into the anterior chamber. The head of the patient and the microscope are both tilted 45° and 35°, respectively. A surgical gonioscopy lens is used to visualize the nasal trabecular meshwork. A 25-G angled needle tip is inserted in the eye (Fig. 3A), and a 90° goniotomy is performed in the superonasal, nasal, and inferonasal quadrants (Fig. 3B). Viscoelastic is removed from the eye with the use of a bimanual irrigation/aspiration device. The incisions are hydrated with a balanced salted solution and sealed.

**Fig. 3 Fig3:**
[figure not shown]
Surgical steps of BANG. **A** A 25-G angled needle tip is inserted in the eye; **B** the trabecular meshwork is excised in the superonasal, nasal, and inferonasal sectors, completing 90° of treatment

After surgery, a fixed combination of topical dexamethasone 1% s and moxifloxacin 5% drop every 4 h will be prescribed for the first week. After this period, the use of antibiotics will be interrupted, whereas steroids will be tapered during the first postoperative month.

If the patient has both eyes eligible for the study, a different procedure will be performed in each eye. The eye with the highest IOP will be operated first, and the second eye will be operated within a week.

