### Statistical analysis plan

The normality of the data will be assessed by the Shapiro–Wilk test. Comparison of longitudinal changes in IOP or the number of medications within a group will be done by Student’s paired *t*-test or the Wilcoxon rank sum test depending on the distribution of the data. The comparison of the above-mentioned parameters between the groups will be done by a non-paired Student’s *t-*test or the Mann–Whitney-*U* test depending on the distribution of the data. Categorical variables will be compared using the chi-square or the Fisher exact test.

A Kaplan–Meier survival curve will also be used to compare the success rates of both procedures. Complete success is defined as an IOP reduction ≥ 20% from baseline under no antiglaucoma medication at the final 12-month visit. Qualified success is defined as an IOP reduction ≥ 20% from baseline with the use of medication, but no increase in medication compared to the recruitment visit. Failure is defined as an IOP reduction < 20% from baseline, the need of additional glaucoma surgery to control IOP, IOP < 5 mmHg with the evidence of hypotony maculopathy, or persistent BCVA equal or lower to light perception. The log-rank test will be used to compare the survival curves of both procedures. *P* values < 0.05 will be considered statistically significant.

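### Fellow eyes of bilateral patients go to opposite arms, but the between-arm tests treat all eyes as independent, which makes them conservative and costs power

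*Protocol article*

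**What the plan says.** The Setting section makes the eye the unit of allocation: "eyes will be randomized to BANG or GATT by a sealed envelope at a 1:1 ratio". The sample size is also counted in eyes.

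Under Interventions, the article adds a rule for patients with two eligible eyes: "If the patient has both eyes eligible for the study, a different procedure will be performed in each eye". On order and timing it says: "The eye with the highest IOP will be operated first, and the second eye will be operated within a week".

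The Statistical analysis plan section then fixes these tests:

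- **IOP and number of medications, between arms:** "The comparison of the above-mentioned parameters between the groups will be done by a non-paired" Student's t-test or the Mann–Whitney U test.
- **Categorical outcomes:** "Categorical variables will be compared using the chi-square or the Fisher exact test".
- **Success over time:** "The log-rank test will be used to compare the survival curves of both procedures".

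A paired t-test is named only for change over time within one arm: "Comparison of longitudinal changes in IOP or the number of medications within a group will be done by" that test or a rank-based alternative. The article states no mixed model, GEE, clustered or stratified test, or one-eye-per-patient rule. The Sample size calculation section makes no allowance for correlation between eyes.

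**The concern.** The design creates pairs across the arms and the analysis ignores them. Two eyes of one patient share age, systemic factors, adherence and disease biology, so their IOP changes are likely to be positively correlated. One eye is in each arm, so the shared part cancels when the arm means are subtracted. A non-paired test does not credit that cancellation: it reports the standard error that would apply if all eyes came from different people.

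This touches the primary outcome, IOP reduction, as well as the medication, categorical and success comparisons. What is at stake is precision. Intervals come out wider and P values larger than the data justify, and a real difference between the procedures is more easily missed. The Discussion says the results could help surgeons choose between the two procedures, so a non-significant result might be read as the two performing alike.

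**Working it through.** **Inputs from the article.** Difference 3 mmHg, SD 5 mmHg, 80% power, 45 eyes in total (Sample size calculation); significance at P < 0.05 (Statistical analysis plan), read as two-sided; 1:1 allocation (Setting).

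**Assumed, because the article does not give them.** The number of bilateral pairs m (0, 2, 4, 11, 22) and the correlation ρ between fellow eyes (0.5, range 0.3 to 0.7). The SD of 5 is taken as the per-eye SD of the analysed outcome.

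**The article's own figure first.** Two independent groups need 2 × [5 × (1.96 + 0.842) / 3]² = 43.6, so 44 eyes per arm (88 in total) by normal approximation, or 45 per arm (90) by the exact t calculation. The stated total of 45 is not reproduced. At 45 eyes in total (22 and 23), the non-paired t-test has about 50% power (52% by normal approximation). That shortfall is a separate issue and is used here only as the baseline.

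**Standard errors.** With n₁ = 22 and n₂ = 23:

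- Reported by the non-paired test: 5 × √(1/22 + 1/23) = 1.49.
- True variance of the difference: 25 × (1/22 + 1/23) − 2mρ × 25 / (22 × 23).
- For m = 11, ρ = 0.5: 2.223 − 0.543 = 1.680, so the true SE is 1.30. For ρ = 0.3 it is 1.38, and for ρ = 0.7 it is 1.21.

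**Type I error, normal approximation.** For m = 11, ρ = 0.5, the nominal cut-off of 1.96 acts as 1.96 × 1.491 / 1.296 = 2.25, which gives 2.4%. Simulation of the t-test gives about 2.5%.

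**Power when the correlation is used.** Information about the difference adds over pairs and single eyes: m / [2 × 25 × (1 − ρ)] + 1 / [25 × (1/s₁ + 1/s₂)], where s₁ and s₂ are the single eyes per arm. For m = 11, ρ = 0.5: 11/25 + 1 / [25 × (1/11 + 1/12)] = 0.440 + 0.230 = 0.670. The SE is 1/√0.670 = 1.22, and power is Φ(3/1.22 − 1.96) = 69%.

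**Results at ρ = 0.5** (type I error and non-paired power by simulation of the t-test; last column by normal approximation):

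| Pairs | SE reported | SE true | Type I error | Power, non-paired | Power, pairing used |
|---|---|---|---|---|---|
| 0 | 1.49 | 1.49 | 5.0% | about 50% | 52% |
| 2 | 1.49 | 1.46 | about 4.6% | about 50% | 56% |
| 4 | 1.49 | 1.42 | about 4.1% | about 50% | 59% |
| 11 | 1.49 | 1.30 | about 2.5% | about 50% | 69% |
| 22 (44 eyes) | 1.51 | 1.07 | about 0.7% | about 50% | 80% (77% by exact paired t) |

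For 11 pairs, over ρ = 0.3 to 0.7, type I error runs from about 3.5% to 1.7% and power with the pairing used from 60% to 84%. The first row shows that about 2 points of the gap between the last two columns come from the normal approximation, not from the pairing.

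The chi-square, Fisher and log-rank comparisons rest on the same independence assumption. Their loss is in the same direction but was not sized.

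**The case against.** The strongest reply is that the error is on the safe side and may be small. Both parts stand. With fellow eyes in opposite arms and a positive correlation, the planned tests reject too rarely, so a significant result remains credible. The number of pairs is unknown. Each fellow eye must separately be pseudophakic, have IOP of at least 18 mmHg twice on at most three medications, reach 20 to 36 mmHg after washout, and meet the visual field and nerve fibre layer limits. Few pairs is as compatible with the text as many, and with none the problem disappears.

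It cannot be said that the matter is simply left to an unseen plan, because the article itself names the non-paired test.

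Some stronger readings are tempting, and the documents do not support them:

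- **The trial risks false-positive claims.** The direction is the opposite.
- **The ignored pairing explains the low power.** Non-paired power stays near 50% at every pair count. That baseline comes from the sample size; only the forgone gain belongs here.
- **The 45 eyes were planned as pairs.** [5 × 2.80 / 3]² = 21.8 gives 22 pairs, or 44 eyes, which is close. But this needs every patient to be bilateral and a paired analysis, and the article states neither.
- **Each bilateral patient pulls the quality-of-life comparison to zero.** The article lists "functional, structural, and quality of life evaluation" among the secondary outcomes but states no between-arm test for quality of life. The sentence on non-paired tests refers back to IOP and number of medications. Nor need the scores be identical, since the eyes may be operated up to a week apart and visits are counted from surgery.
- **The second eye can be selected with its arm known.** That is a separate question of concealment. It is partly covered, because eligibility and washout precede allocation and the highest-IOP-first rule requires both eyes to be assessed beforehand.

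**Conclusion.** The point holds as a mismatch between the allocation rule and the stated between-arm tests. Its consequence is conservative inference and lost power. It ranges from nothing (no pairs), through a small loss (2 to 4 pairs: type I error about 4.6% to 4.1%, power about 50% against 56% to 59%), to a material one (11 pairs: type I error about 2.5%, power about 50% against 69%). In the extreme of 22 pairs, type I error is about 0.7% and power about 50% against 77% by exact paired t.

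These figures rest on SD 5, a 3 mmHg difference and an assumed correlation of 0.5. The article supplies neither the correlation nor the number of pairs. It does provide explicitly for bilateral patients, so the analysis should allow for them. Severity: should be fixed; the primary comparison is not invalidated in the direction of false claims.

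**What to change.** State the patient as the cluster in every between-arm comparison:

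- **IOP and number of medications:** a linear mixed model with a patient random effect, or GEE clustered on patient, so that paired and single eyes both contribute.
- **Categorical outcomes:** GEE clustered on patient, where the numbers allow.
- **Time to failure:** a marginal Cox model or a log-rank test with patient-clustered robust variance.

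Report how many patients contribute two eyes.

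The cost is a slightly more complex analysis that needs small-sample care (degrees of freedom, robust variance with few clusters). No new data are required: patients already receive an identification number at recruitment. The article describes recruitment as still open, so the change could be specified before analysis. If few patients turn out to be bilateral, little is lost.

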### Follow-up

Patients will be followed 1, 7, 15, 30, 60, 90, 180, 330, and 360 days after surgery (Table 1). In all visits, BCVA and IOP will be measured. Additional visits may be scheduled at the surgeon’s discretion. If in two consecutive visits, the IOP is higher than 18 mmHg, a topical carbonic anhydrase inhibitor will be introduced; if IOP remains above 18 mmHg, the introduction of a second-class IOP-lowering medication will be considered. At visit 330, a new medication washout will be done, and patients will be instructed to interrupt all medications in the operated eye until visit 360.

**Table 1 Tab1:** Procedures at each timepoint

	**Enrolment**	**Allocation**	**Post-allocation**						**Close-out**
Timepoint**	*** − t***_***1***_	**0**	***t***_***1***_	***t***_***2***_	***t***_***3***_	***t***_***4***_	***t***_***5***_	***t***_***6***_	***t***_***7***_
Description	*** − 30 days***	**0**	***1DPO***	***7DPO***	***30 DPO***	***90 DPO***	***180 DPO***	***330 DPO***	***360 DPO***
Enrolment									
* Eligibility screen*	X								
* Informed consent*	X								
* Allocation*		X							
Interventions									
* Surgery (GATT)*		X							
* Surgery (BANG)*		X							
Assessments									
* Intraocular pressure*	X		X	X	X	X	X	X	X
* Medication use*	X		X	X	X	X	X	X	X
* Functional, structural, and quality of life evaluation*	X				X	X	X		X
* Adverse effects*			X	X	X	X	X	X	X

*DPO* Day postoperative, *GATT* Gonioscopy-assisted transluminal trabeculotomy, *BANG* Bent ab interno needle goniotomy

At visits 30, 90, 180, and 360, all exams obtained at baseline for structural, functional, and quality of life assessment will be repeated. After completing the study endpoint, patients will continue the regular follow-up at the two glaucoma centers enrolled in this study.

During the follow-up period, the investigators will be in close contact with participants (telephone and/or message) to assess any change in visual status. If any change is referred by the participant, a visit will be scheduled for re-evaluation.

Participants will be allowed to withdraw from the study at any time without justification. If possible, patients will be asked to attend for a visit 12 months after surgical intervention to evaluate IOP. Patients who decide to withdraw from the study will be allowed to continue the regular follow-up at the Glaucoma Sector of the recruiting centers without any prejudice.

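### A within-arm fall in drug count cannot be credited to surgery, because the entry count and the post-operative count follow different prescribing rules

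*Protocol article*

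**What the plan says.** All references are to the protocol article.

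- **Entry.** The Inclusion and exclusion criteria require an IOP of at least 18 mmHg "under a maximum of 3 IOP-lowering medications", and "IOP between 20 and 36 mmHg after medication washout".
- **First washout.** After consent, "patients will be asked to interrupt the use of all IOP-lowering medications" for 30 days (Participant recruitment section, text after Fig. 1). The drug count is therefore zero at surgery.
- **Post-operative ladder (Follow-up).** "If in two consecutive visits, the IOP is higher than 18 mmHg", then "a topical carbonic anhydrase inhibitor will be introduced". If IOP stays above 18 mmHg, "the introduction of a second-class IOP-lowering medication will be considered". No further step is named.
- **Second washout (Follow-up).** All drugs in the operated eye are stopped from day 330 to day 360.
- **Masking.** Only participants are masked (Randomization and group allocation). The Limitations section acknowledges that investigators are unmasked in follow-up.
- **Outcome and tests.** The Setting section states: "Secondary outcomes are a reduction from baseline of medication use", among others. The Statistical analysis plan tests the number of medications within each group (paired t-test or Wilcoxon) and between groups (unpaired t-test or Mann-Whitney). Qualified success requires "no increase in medication compared to the recruitment visit".

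**The concern.** The two counts being compared arise under different rules. The recruitment count reflects earlier prescribing and may be as high as three. The post-operative count starts from zero and rises only as the ladder adds drugs, first by rule and then by judgement. Their difference mixes any effect of surgery with the change of rule.

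The within-arm test asks whether the count changed, and it can reject when surgery had no effect. A significant fall could then be reported as a drug-sparing benefit of BANG, of GATT or of both. Between arms the rule is common, but the second step is discretionary and the people applying it know the arm, so the contrast can carry their prescribing habits. The article's own Strengths section faults earlier studies for not isolating what MIGS does to IOP and medications, so a clean medication result matters to the trial's stated purpose.

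**Working it through.** The plan gives no figure for the medication outcome, so there is none to reproduce. The check follows an eye in which surgery had no effect.

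**Inputs from the article:** entry on 0 to 3 drugs; off-drug IOP of 20 to 36 mmHg; trigger above 18 mmHg at two consecutive visits; one class introduced by rule; a second class considered.

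**Assumptions:** the reference count is the one at recruitment, as in the qualified-success definition; prescribing stays on the named steps; *q* is the share of eyes that end on a second drug. The article does not give *q*, so 0, 0.5 and 1 are shown.

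**Step 1.** With no surgical effect, off-drug IOP stays at 20 mmHg or more. That is above 18, so the first drug is always triggered.

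**Step 2.** Expected post-operative count = 1 + *q*.

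**Step 3.** Built-in reduction = entry count − (1 + *q*). A negative value is an increase.

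| Entry count | q = 0 | q = 0.5 | q = 1 |
|---|---|---|---|
| 3 | 2 | 1.5 | 1 |
| 2 | 1 | 0.5 | 0 |
| 1 | 0 | −0.5 | −1 |
| 0 | −1 | −1.5 | −2 |

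**Step 4.** Arm mean = mean entry count − (1 + *q*). The entry mixes are assumed, because the article gives only the maximum.

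| Share on 1 / 2 / 3 drugs | Mean entry count | q = 0 | q = 0.5 | q = 1 |
|---|---|---|---|---|
| 0 / 0 / 100% | 3.0 | 2.0 | 1.5 | 1.0 |
| 0 / 50 / 50% | 2.5 | 1.5 | 1.0 | 0.5 |
| 20 / 30 / 50% | 2.3 | 1.3 | 0.8 | 0.3 |
| 20 / 40 / 40% | 2.2 | 1.2 | 0.7 | 0.2 |
| equal thirds | 2.0 | 1.0 | 0.5 | 0.0 |
| 50 / 30 / 20% | 1.7 | 0.7 | 0.2 | −0.3 |

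The built-in change is a reduction only when the mean entry count exceeds 1 + *q*. It is zero when they are equal and an increase when the entry count is lower.

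**Step 5, between arms.** With the same ladder and the same *q*, the term 1 + *q* cancels. If *q* differs between arms by 0.25, the contrast shifts by 0.25 drug among eyes that reach the second step.

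**Step 6, qualified success.** Eyes on the named steps use at most two drugs. An eye that entered on 2 or 3 then meets the no-increase condition whatever surgery did. It would fail that condition only if prescribing went beyond the named steps.

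**Step 7, choice of visit.** An eye that follows the second washout uses no drugs at day 360. A count taken then would show a reduction equal to the whole entry count, so day 360 cannot serve for this outcome.

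**The case against.** Five points can be made for the plan.

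1. **No cap is stated.** A reader might infer that eyes cannot receive a third drug, so that eyes entering on 2 or 3 can never break the no-increase clause. The article does not support this. It names two steps and bars nothing further, and a condensed article may leave later steps to the full protocol. The clause is weak for these eyes but not impossible to break. This objection stands.
2. **The direction is not fixed.** A reader might infer that a reduction is built in for the trial as a whole. It is not: lighter entry mixes give zero or an increase. This stands too, but it does not rescue the within-arm test, because a change of unknown sign and size unrelated to surgery still makes that test uninterpretable.
3. **Both arms share the ladder.** This is correct, and the ladder alone favours neither procedure. A between-arm bias needs different use of the discretionary step. The documents make that possible but do not show that it happens.
4. **Unmasked follow-up is disclosed.** It is, as a general limitation. The disclosure does not connect it to the medication outcome.
5. **Uncontrolled eyes are caught elsewhere.** The failure definition covers an IOP reduction below 20% and the need for further glaucoma surgery, and IOP at day 360 is read after the second washout. The point therefore does not reach the final off-drug IOP result. It concerns the drug count, which has its own place among the secondary outcomes.

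**Conclusion.** The point holds for the medication outcome. On the named steps, an eye with no surgical effect records 1 to 2 fewer drugs from an entry count of 3 and 0 to 1 fewer from 2. From 1 it records 0 to 1 more, and from 0 it records 1 to 2 more. Over the assumed mixes the arm mean lies between a reduction of 2.0 and an increase of 0.3. These sizes rest on the assumed mix, on an unknown *q*, on the recruitment count as reference and on prescribing that stays on the two named steps.

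The within-arm test therefore cannot attribute a change in drug count to surgery. The between-arm comparison is sounder, since the ladder is common, but it carries unmasked discretion at the second step. This is a correction to one secondary outcome that should be made; it does not undermine the trial.

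**What to change.** In the Statistical analysis plan section:

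1. Treat the within-arm change in number of medications as descriptive, and draw no efficacy conclusion from it.
2. Base the medication conclusion on the between-arm comparison at the last visit before the day-330 washout takes effect.
3. Report beside it, by arm, the share of eyes above 18 mmHg at two consecutive scheduled visits, and the share still above 18 mmHg on whatever drugs they use at that last pre-washout visit. The second share includes eyes left on one drug as well as those on two. The restriction to scheduled visits matters because the surgeon may add visits, which changes the chance of meeting the trigger. IOP readings remain unmasked, so these shares support the count but do not remove all judgement.

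The Inclusion and exclusion criteria, Follow-up and Statistical analysis plan sections should also be reconciled on how many drugs may be in use after surgery. This review proposes no rule.

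The cost is wording and a few more lines in the results. IOP and medication use are already collected at every post-operative visit in Table 1. The downside is small: the medication result may look less favourable and needs slightly more reporting.
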